**PROs^h^**			
	Symptoms: snoring, excessive daytime sleepiness, daytime fatigue, lack of energy, waking up feeling tired, poor sleep, falling asleep at the wheel, nocturia, abrupt awakening with choking and gasping, morning headache, irregular breathing during sleep, decreased libido, depression, anxiety, irritability, and memory or concentration difficulties	Before and after starting PAP therapy	ePRO tool
	Quality of life using the EQ-5D-5L [32]	At the time of ePRO completion	ePRO tool
**OSA and PAP literacy**			
	Perceived and actual competence related to disease literacy and PAP use assessed using 13 variables with binary responses	At the time of ePRO completion	ePRO tool
**Experience and satisfaction with PAP therapy**			
	Measured using a visual analogue scale for Difficulty tolerating PAP (discomfort related to pressure, and mask) Likelihood of continued use Perceived health benefits Global satisfaction Noise acceptance/impact Motivation to use	At the time of ePRO completion	ePRO tool
**Experience and satisfaction with home support provider**			
	Measured using a 5-point Likert scale for Home support provider availability for logistical support Home support provider availability for educational support Satisfaction with home support provider Perceived value of home support provider	At the time of ePRO completion	ePRO tool
**Characteristics of PAP therapy**			
	Type of PAP device and mask	At the start of PAP therapy	ALH ERP
	Elevated apnea-hypopnea index Elevated unintentional leaks	1, 4, 6, and 12 months after starting PAP therapy and annually thereafter	Device data
**Home support provider PAP-related service**			
	Number and type of interactions (home visit, phone call, and digital interaction) Number of mask changes Implementation of telemonitoring	1, 4, 6, and 12 months after starting PAP therapy and annually thereafter	ALH ERP
**PAP adherence**			
	Mean number of hours per day of PAP use Mean PAP use categorized as: 0-2 hours/day, 2-4 hours/day, 4-6 hours/day, and ≥6 hours/day Proportion of adherent patients defined as (1) mean PAP use ≥4 hours/day, (2) mean PAP use ≥4 hours/day on ≥70% of days, and (3) mean PAP use ≥4 hours/day on ≥80% of days	1, 4, 6, and 12 months after starting PAP therapy and annually thereafter	Device data
**PAP persistence**			
	Percentage of days with or without PAP use defined as the ratio between the number of days with PAP usage (starting from 1 minute of use) over the number of days in the follow-up period Patients without PAP discontinuation (still in therapy), with temporary discontinuation, or with permanent discontinuation Patients still in therapy and with mean PAP use ≥4 h/day	4, 6, and 12 months after starting PAP therapy and annually thereafter	Device data and ALH ERP

^a^OSA: obstructive sleep apnea.

^b^PAP: positive airway pressure.

^c^ALH: Air Liquide Healthcare.

^d^ERP: Enterprise Resource Planning.

^e^ePRO: electronic patient-reported outcome.

^f^GORD: gastro-esophageal reflux disease.

^g^COPD: chronic obstructive pulmonary disease.

^h^PRO: patient-reported outcome.

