## Introduction

Obstructive sleep apnea (OSA) is the most prevalent form of sleep-disordered breathing, affecting nearly 1 billion adults aged 30-69 years worldwide [1]. OSA is characterized by repetitive collapse of the upper airway during sleep, resulting in complete (apnea) or partial (hypopnea) airway obstruction [2]. OSA can cause daytime symptoms that impair quality of life and has been linked with a variety of cardiometabolic diseases, neurocognitive impairment, depression, road traffic accidents, and all-cause mortality [3-12]. Identification and management of OSA are therefore important to reduce those risks.

Positive airway pressure (PAP) therapy remains the gold standard treatment for severe OSA because high-quality evidence and long-term assessment are lacking for noncontinuous PAP therapies [13,14]. PAP therapy has been shown to reduce road traffic accidents, blood pressure, cardiovascular risk, and health care use [15-19]. However, the effectiveness and cost-effectiveness of PAP therapy are linked to sufficient daily device use, with regular and continued long-term usage [16,19-24], which appears challenging in all geographies [25,26].

In most European countries, home support provider companies supply the PAP device and support its use by the patient. However, the type and level of services provided differ markedly between countries. Services can range from mainly logistical support (ie, device delivery in Belgium, Germany, and the Netherlands) to a personalized support plan for patients integrating motivational interviews to enhance adherence (as in some regions of Spain and Portugal) [27-29]. Also, the number of regulated home visits varies from none to several per year (like in France and Portugal). The use of PAP telemonitoring also varies widely, being routine for almost all patients in France throughout the PAP treatment period [30] but not used (or only used in the first months of therapy or in specific situations) in other countries. Criteria for the reimbursement of PAP therapy also differ markedly between European countries and are likely to influence adherence and persistence. For example, while the fees paid to the home support providers in France increase as the number of hours of PAP use increases [30,31], in Belgium and Germany, nonadherence can result in the cessation of patient reimbursement.

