### Outcome Measures

Study outcomes, time points, and data sources are summarized in Table 1. An ePRO tool will be used to administer the patient questionnaire. The ePRO tool was designed to assess various aspects of a patient’s status, condition, and experience at 2 time points: the time of ePRO completion and the beginning of PAP therapy. This included sociodemographic characteristics (age, relationship status, employment, education level, and social support), health status (BMI, smoking status, alcohol intake, comorbidities, sleep duration, and use medications to aid sleep), OSA-related factors (when PAP therapy was started, apnea-hypopnea index before starting PAP, and OSA symptoms), PAP therapy experience and satisfaction (tolerability of PAP, attitude to PAP, device noise, and level of motivation to use PAP), patient experience and satisfaction with home support providers, quality of life (including current health status), and OSA-PAP literacy. The full ePRO questionnaire is provided in Multimedia Appendix 1.

Home support provider service will be assessed using 4 components: frequency of interactions between the home support provider and a patient; content of support (logistical, educational, supportive, or behavioral); personalization of support according to patient profile or needs; and telemonitoring (telemetry, data visualization, and alerts triggering home support provider interventions).

**Table 1 table1:** Study outcomes.

Category and outcome		Time points	Source

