### Data Sources, Flow, and Management

Potential participants will be identified by applying the inclusion criteria to the data sourced from the ALH Enterprise Resource Planning (ERP) systems. Initially, potential participants will receive an email or SMS invitation to connect to a secure platform for the consent process. Those who provide consent will be granted access to the ePRO tool and will be invited to complete the questionnaire, which takes about 10 minutes.

The study database will be created from 3 data sources: the ALH ERP systems that contain data routinely collected for PAP-related services; the database containing information about PAP device use (collected remotely through the Internet of Things or by download from device memory cards during home provider support visits); and the ePRO tool. Database structure and content will be standardized across countries.

Because the ALH ERP and PAP device use databases are primarily designed for administrative, logistical, and patient follow-up purposes, rather than research, all data will undergo thorough review for completeness, accuracy, and reliability before statistical analysis. These reviews will be conducted in accordance with a detailed data management plan, involving multiple experts with complementary areas of expertise. All decisions made during the review process will be fully documented.

All identifiable personal information will be protected and stored in the study database in pseudonymized form so that it cannot be viewed by the study sponsor or any external vendors that are processing the study data. A summary of data sources and data flow is provided in Figure 1.

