#### Statistical Analysis

Statistical analyses will be performed according to a predefined statistical analysis plan (Table 2).

**Table 2 table2:** Statistical analysis plan details.

Objectives	Main outcomes	Key explanatory variables	Statistical methods
Compare PAP^a^ adherence and the PAP therapy persistence rate between different levels of home support provider service	PAP adherence: (1) mean number of hours/day of PAP use and (2) adherent patients defined as those with mean PAP use ≥4 hours/day PAP persistence: (1) percentage of days with PAP use, (2) patients still in therapy, and (3) patients still in therapy and adherent	Fixed effect: Level of service (standard of care, personalized care plan, or high service level) Random effect: Country	Multilevel model adjusted for selected confounding factors
Identify service components that influence PAP adherence and persistence	PAP adherence: (1) mean number of hours/day of PAP use and (2) adherent patients defined as those with mean PAP use ≥4 hours/day PAP persistence: (1) percentage of days with PAP use, (2) patients still in therapy, and (3) patients still in therapy and adherent	Fixed effect: Frequency of interactions, content of support, personalization of support, and telemonitoring Random effect: Country	Multilevel model adjusted for selected confounding factors
Identify factors associated with PAP adherence and persistence	PAP adherence: (1) mean number of hours/day of PAP use and (2) adherent patients defined as those with mean PAP use ≥4 hours/day PAP persistence: (1) percentage of days with PAP use, (2) patients still in therapy, and (3) patients still in therapy and adherent	Fixed effect: Frequency of interactions, content of support, personalization of support, telemonitoring, sociodemographic characteristics, OSA^b^-related clinical characteristics, and characteristics of PAP therapy Random effect: Country	Multilevel model
Descriptive Analysis	Sociodemographic characteristics OSA-related clinical characteristics OSA and PAP literacy Experience with PAP therapy Experience with home support provider support Quality of life Home support provider PAP-related service	N/A^c^	Usual descriptive statistics: Analysis by country
Describe patterns of PAP use	Mean PAP use categories over time	N/A	Data visualization such as Sankey diagrams

^a^PAP: positive airway pressure.

^b^OSA: obstructive sleep apnea.

^c^N/A: not applicable.

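### The percentage-of-days persistence outcome cannot separate a day without PAP use from a day without retrieved device data, and retrieval depends partly on the service components under test

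*Protocol article*

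**What the plan says.** Table 1 of the protocol article (PAP persistence) sets the percentage-of-days measure by this rule: "ratio between the number of days with PAP usage (starting from 1 minute of use) over the number of days in the follow-up period". A day is either with or without use, and there is no third state for a day whose data are unavailable. The length of follow-up that forms the denominator is not defined further.

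Table 2 (Statistical Analysis) lists the outcomes to be modelled as "PAP persistence: (1) percentage of days with PAP use, (2) patients still in therapy, and (3) patients still in therapy and adherent". They are compared across service levels and, in a second model, across service components entered as fixed effects, with country as a random effect.

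Under Outcome Measures, two of the four service components are "frequency of interactions between the home support provider and a patient" and "telemonitoring (telemetry, data visualization, and alerts triggering home support provider interventions".

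Under Data Sources, Flow, and Management, device-use data are "collected remotely through the Internet of Things or by download from device memory cards during home provider support visits". No third route is named.

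The Introduction describes telemonitoring as "being routine for almost all patients in France throughout the PAP treatment period". Its account of the situation elsewhere reads: "but not used (or only used in the first months of therapy or in specific situations) in other countries". It also says that "the number of regulated home visits varies from none to several per year".

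**The concern.** Whether a day of use can enter the numerator depends on whether the device transmitted, or on whether someone visited and downloaded the card. Both belong to the service being evaluated. The model therefore regresses an outcome on part of the process that makes the outcome visible. Two patients with identical use can score differently because one is telemonitored and the other is not.

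None of the planned safeguards addresses this:

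- The country random effect does not correct differences in capture between telemonitored and other patients within a country.
- The e-value concerns unmeasured confounders, not how the outcome is ascertained.
- The sensitivity analyses cover lockdown periods and the device recall.
- The Limitations section does not mention service-dependent capture of device data.

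The results are meant to inform payers and authorities on services and tariffs (Study Rationale). An apparent benefit of telemonitoring or visits that partly reflects data retrieval would therefore matter.

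**Working it through.** The article gives no figure for this outcome and no coverage figure, so there is nothing of the plan's own to reproduce. The calculations below illustrate the written rule under stated assumptions.

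**Inputs.** From the article: numerator, denominator, the two retrieval routes, and about 100,000 expected patients (Sample Size). Assumed: true use *u* of 85% or 70% of days, share of follow-up days with retrieved data (coverage) *c*, depth of card memory, and an SD of 30 points.

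**Step 1: the literal rule.** If retrieval is unrelated to use, the observed ratio is *u* × *c* and the loss is *u* × (1 − *c*).

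| True use | Coverage | Observed | Loss |
|---|---|---|---|
| 85% | 100% | 85% | 0 |
| 85% | 90% | 0.85 × 0.90 = 76.5% | 8.5 points |
| 85% | 60% | 0.85 × 0.60 = 51% | 34 points |
| 70% | 90% | 0.70 × 0.90 = 63% | 7 points |
| 70% | 60% | 0.70 × 0.60 = 42% | 28 points |

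Two groups with the same true use but different coverage differ by *u* times the coverage difference.

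**Step 2: what coverage could be.** Without telemonitoring, yearly coverage from evenly spaced visits is visits × card depth / 365, capped at 1.

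- Depth 365 days, one visit: 365/365 = 100%.
- Depth 90 days, one visit: 90/365 = 25%.
- Depth 90 days, four visits: 360/365 = 99%.
- No visit and no telemonitoring: 0% at any depth.

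The article gives neither card depth nor visits per patient, so coverage could lie anywhere in this range.

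**Step 3: would a small artefact be noticed as an effect?** Take a simple two-group comparison of 100,000 independent patients at two-sided 5%, with a purely artefactual gap of 1 point.

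- Equal split: SE = 30 × √(2/50,000) = 0.19, and the probability of significance is above 99%.
- Split 10:90: SE = 30 × √(1/10,000 + 1/90,000) = 0.32, and the probability is 88.5%.

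**Step 4: is a retrieved-days denominator enough?** Suppose coverage is 60%, with use on 85% of retrieved days and 40% of the others.

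- Truth: 0.60 × 0.85 + 0.40 × 0.40 = 0.51 + 0.16 = 67%.
- All follow-up days: 0.60 × 0.85 = 51%.
- Retrieved days only: 85%.
- Bounds with missing days all unused or all used: 51% to 0.51 + 0.40 = 91%. These contain the truth.

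Neither denominator alone is safe when retrieval relates to use. The bounds are as wide as the uncovered share, here 40 points. At 90% coverage they would be 10 points wide.

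**The case against.** The strongest reply is that this is one line in a summary table. A predefined analysis plan and a detailed data management plan are cited, and neither is shown. Completeness is to be reviewed before analysis, and no sentence says that unretrieved days are scored as non-use. This stands in part: the fuller documents may contain a rule, and its absence from an article is not a fault. But the article does state a denominator. A plan that handled unretrieved days properly would have to replace that denominator, not merely supplement it. A completeness review can find gaps but does not change the ratio.

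Four stronger readings are tempting, and the document does not support them.

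- *Days in low-service areas were not recorded.* Cards store past use and a later download can recover it. The accurate description is not retrieved, and with deep memory and a yearly visit the loss could be nil.
- *Low-service patients will look non-persistent, in favour of the study hypothesis.* Service level is not the same as data coverage. The Introduction places near-universal telemonitoring in France but personalised plans with motivational interviews in some regions of Spain and Portugal, so the artefact could run against the hypothesis. If unretrieved days or patients were excluded instead, the bias could reverse.
- *The difference is some tens of points.* That requires assumed coverages for which the document offers no basis.
- *All persistence results are affected.* Only one of the three modelled persistence outcomes is this ratio, and the persistence row also draws on the ERP. The adherence definitions based on 70% and 80% of days are not among the main modelled outcomes.

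The coverage contrasts in the Introduction are also mostly between countries, and the random effect may absorb part of them. The analysis of service components stays exposed within countries.

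**Conclusion.** The point holds for the percentage-of-days outcome. As written, it merges days without use with days without retrieved data, while retrieval runs through telemonitoring and visits, which belong to the tested exposure. Under the literal rule, telemonitoring and more frequent visits can appear to raise persistence without any effect on use.

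The size cannot be determined from the article. The losses of 8.5 points at 90% coverage and 34 points at 60% rest on assumed true use of 85% and on retrieval unrelated to use. At the planned sample size even a 1-point artefact would probably reach significance, given an SD of 30 points and independent patients. For telemonitoring and visit frequency, the direction follows from the literal rule. Across the three overall service levels it is not established.

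**What to change.** Change the definition in Table 1 and carry it into the analysis plan:

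1. Denominator: days with retrieved device data while in therapy, plus days after permanent discontinuation confirmed in the ERP, with the latter counted as non-use.
2. Treat all other unretrieved days as missing.
3. Report the share of days retrieved by country, service level and telemonitoring status.
4. Because the new denominator can itself be biased when retrieval relates to use, add a sensitivity analysis that scores unretrieved in-therapy days first as all used and then as all unused. State whether the service comparisons survive both.

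This needs no new data collection. The cost is some extra analysis, and less precise estimates with wide bounds where coverage is low.

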### Data Sources, Flow, and Management

Potential participants will be identified by applying the inclusion criteria to the data sourced from the ALH Enterprise Resource Planning (ERP) systems. Initially, potential participants will receive an email or SMS invitation to connect to a secure platform for the consent process. Those who provide consent will be granted access to the ePRO tool and will be invited to complete the questionnaire, which takes about 10 minutes.

The study database will be created from 3 data sources: the ALH ERP systems that contain data routinely collected for PAP-related services; the database containing information about PAP device use (collected remotely through the Internet of Things or by download from device memory cards during home provider support visits); and the ePRO tool. Database structure and content will be standardized across countries.

Because the ALH ERP and PAP device use databases are primarily designed for administrative, logistical, and patient follow-up purposes, rather than research, all data will undergo thorough review for completeness, accuracy, and reliability before statistical analysis. These reviews will be conducted in accordance with a detailed data management plan, involving multiple experts with complementary areas of expertise. All decisions made during the review process will be fully documented.

All identifiable personal information will be protected and stored in the study database in pseudonymized form so that it cannot be viewed by the study sponsor or any external vendors that are processing the study data. A summary of data sources and data flow is provided in Figure 1.

**Figure 1 figure1:**
[figure not shown]
Diagram of data sources and data flow. AHI: apnea-hypopnea index; ALH: Air Liquide Healthcare; ePRO: electronic patient-reported outcome; ERP: Enterprise Resource Planning; HSP: home support provider; IoT: Internet of Things; PRE: patient-reported experience; QoL: quality of life.

### Statistical Methods

#### Sample Size

This study aims to include all adults starting PAP therapy managed by an ALH home support provider in the participating countries who met the selection criteria during the study time period. This approach minimizes selection bias and sampling errors, ensuring precise and reliable results. Inclusions will be possible at the national level (France) or only at some investigational sites in countries requiring regional or hospital-level regulatory processes. All potential participants will be informed whenever ethics committee approval is obtained from the respective regions or hospitals. It is expected that around 30% of the 150,000 eligible participants will not be enrolled due to the absence of (or incorrect) email, or refusal to participate. Therefore, the number of included patients is expected to be around 100,000. With a sample of this size, the probability of showing a statistically significant difference in adherence between different levels of service if one exists is >99%, even if there were important imbalances between groups.

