## Abstract

**Background:**

Adherence and persistence to positive airway pressure (PAP) therapy are key factors for positive health outcomes. Home support providers participate in the home implementation and follow-up of PAP therapy for patients with obstructive sleep apnea (OSA). In Europe, home support provider service levels are country (or area) specific, resulting in differences in content and frequency of patient interactions. However, no robust evaluation of the impact of these differences on clinical and patient outcomes has been performed.

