#### Multilevel Models

Individuals living in the same country share a common health care system, lifestyle, and climate, and tend to be more similar than individuals from other countries. Therefore, individuals are considered nested within a country. This correlation of observations violates the assumption of independence for standard regression analysis leading to biased standard errors of parameter estimates. Therefore, we will fit multilevel linear or logistic mixed models using the country variable as a random effect to test the association between adherence or persistence and levels of service while accounting for this nested data structure.

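### The claim of more than 99% power names no difference to detect and rests on patient count alone, although service is set by country or area

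*Protocol article*

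**What the plan says.** **Sample size.** The Sample Size section takes all eligible patients rather than deriving a target number. "It is expected that around 30% of the 150,000 eligible participants will not be enrolled", and "Therefore, the number of included patients is expected to be around 100,000". From that number alone it concludes that "the probability of showing a statistically significant difference in adherence between different levels of service if one exists is >99" per cent, "even if there were important imbalances between groups". It gives no difference, SD, baseline rate, significance level, group sizes, number of areas or ICC.

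**Outcome and model.** In Table 2 adherence has two forms, mean daily hours of use and the proportion averaging at least 4 hours. Service has three levels as a fixed effect, and country is the random effect.

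**Where service varies.** The Abstract says that "home support provider service levels are country (or area) specific". The Introduction contrasts mainly logistical support in Belgium with near-universal telemonitoring in France, and places personalised plans in parts of Spain and Portugal. The Multilevel Models section treats patients as nested within country and says of this: "This correlation of observations violates the assumption of independence for standard regression analysis".

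**Populations.** Patient Datasets separates all included patients from the subset who complete the questionnaire.

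**The concern.** Power is a function of the true difference. A promise of more than 99% for any difference that exists, at any imbalance, cannot be true of any finite sample.

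The second problem lies between two sections. The power statement uses only the number of patients, while Multilevel Models says patients in the same country are not independent. If service is fixed for a whole country or area, more patients in it do not reduce the variation between countries or areas. Information on service level is then limited by the number of units.

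The Discussion says the results should inform payers and authorities on services and tariffs. With this sentence in the protocol, a non-significant result could be taken as strong evidence that service level makes no difference, when some contrasts may have been poorly powered.

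**Working it through.** **1. The plan's own figures.** Enrolment: 150,000 × 0.70 = 105,000, which the article rounds to 100,000. That holds. The 99% figure cannot be reproduced, because its inputs are not given.

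**2. Independent patients (the most favourable case).** Assumed: two-sided alpha 0.05 and SD 2.3 h/day; N = 100,000 is from the article. Difference detectable with 99% power = (1.960 + 2.326) × 2.3 × √(1/n₁ + 1/n₂).

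| Split | √ term × 2.3 | Detectable difference |
|---|---|---|
| 50:50 | 0.01455 | 0.062 h (3.7 min) |
| 95:5 | 0.03337 | 0.143 h (8.6 min) |
| 99:1 | 0.0731 | 0.313 h (19 min) |

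At a true difference of 0.02 h, power with equal groups is Φ(0.02/0.01455 − 1.96) = Φ(−0.59) = 28%.

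For the adherent proportion, assume 70% v 71%. Power = Φ((0.01 − 1.96·SE₀)/SE₁), with SE₀ pooled and SE₁ unpooled. This gives 93% at 50:50, 55% at 90:10, 33% at 95:5 and 10% at 99:1. So the sentence fails without any appeal to clustering, although it would be true for moderate effects: at 0.5 h/day even the 99:1 split exceeds 99%.

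**3. Service set at cluster level.** Assumed: K equal clusters split evenly between two service levels, m = 100,000/K patients each, SD 2.3 and a t-test on K − 2 df. Variance of a cluster mean = 2.3² × (ICC + (1 − ICC)/m); SE of the contrast = √(variance × 4/K).

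- K = 4, ICC 0.01: variance = 5.29 × (0.01 + 0.99/25,000) = 0.0531; SE = 0.2305; 0.5/0.2305 = 2.17 against a critical t of 4.30 on 2 df; power 24%.
- K = 20, ICC 0.01: variance = 5.29 × (0.01 + 0.99/5,000) = 0.0539; SE = 0.1039; 0.5/0.1039 = 4.81 against 2.10 on 18 df; power 99.5%.

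Power for 0.5 h/day:

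| Clusters | ICC 0.005 | ICC 0.01 | ICC 0.05 |
|---|---|---|---|
| 4 (countries, worst case) | 40% | 24% | 9% |
| 8 | 95% | 72% | 21% |
| 12 | above 99% | 92% | 33% |
| 20 | above 99% | 99.5% | 54% |

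For 0.25 h/day at ICC 0.01, power is 10% with 4 clusters and 62% with 20. With a normal test in place of the t-test, the four-cluster figure at ICC 0.01 and 0.5 h is 58%.

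**4. Population.** By Table 1, eight of the listed confounders come only from the questionnaire: sleep duration, symptoms before therapy, occupation, education, bed partner, comorbidities, smoking and alcohol. Where they enter a complete-case model, N is the number of completers, which the article does not forecast. If completion were 50% or 10% (assumed), the equal-group difference in step 2 would grow from 0.062 h to 0.062/√0.5 = 0.088 h or 0.062/√0.1 = 0.20 h.

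**The case against.** The strongest reply is that the four-country calculation is not the study described. Table 2 has three service levels, not two. Service varies within Spain and Portugal, and part of its definition is personalisation to the patient. About 90,000 people had already been informed in France alone, so four equal countries are not expected. For contrasts within a country, the planned country effect absorbs the correlation between compatriots, and the country-level design effect does not apply. This stands. A reader might infer from the worst case that true power is about 24%, or that 100,000 patients are worth only 398 (100,000/251 at ICC 0.01). The documents do not support either as the main case: the number of areas is unknown, and with 20 areas at low ICC the loss for 0.5 h is small. Correlation within areas could still matter, but its size cannot be read from the article.

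A reader might also infer that the protocol declares patients independent, or plans a test that ignores clustering. It does neither. Independence is inferred from a power figure built on patient count alone; the planned analysis is multilevel. A warning that differences of a few minutes will be called significant would therefore describe a patient-level test that is not planned.

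Finally, missing inputs may sit in the full protocol, and no sample size was derived from this figure. Both points are fair. But the article itself states the figure without qualification, and inputs held elsewhere cannot make it true of every difference.

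**Conclusion.** The power sentence is wrong as written. That conclusion needs no assumption about clustering: with independent patients, 99% power is reached only above roughly 0.06 to 0.31 h/day, depending on the split (SD 2.3 h/day assumed). It is also not shown to apply to this design, because it makes no allowance for service being set by country or area.

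The size of that second problem is uncertain. For 0.5 h/day it runs from severe (about 40% down to 9% power with four countries, ICC 0.005 to 0.05) to negligible (above 99% with 20 areas at ICC 0.01), and back to material (54% with 20 areas at ICC 0.05). SD, ICC, number of areas, equal clusters and a two-level contrast are all assumptions. The enrolment arithmetic is sound. Nothing here shows that the study is underpowered overall; it shows that the stated assurance is unsupported.

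**What to change.** Withdraw the 99% sentence. In its place, state the smallest detectable difference, in hours per day and in the adherent proportion:

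- at the level where service actually varies, separately for within-country and between-country contrasts;
- over a stated range of ICC and number of areas, with the four-country case labelled as the worst case;
- for the included population and, where questionnaire-only covariates enter the model, for the expected questionnaire population.

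State the significance level and the SD or baseline rate used. The cost is one paragraph and a less favourable figure; no extra patients are needed.
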